#### Multiple imputation-based sensitivity analyses

We intend to calculate the post-randomization slope only after imputing missing ALSFRS-R data in the 18 months of treatment period and then categorize participants into responders/non-responders and finally conduct logistic regression analysis to estimate the effect of TUDCA. This approach is supported by simulation studies conducted by Floden and Bell [16]. A first sensitivity analysis will be carried out using the multiple imputation (MI) technique under the missing at random (MAR) assumption to deal with missing ALSFRS-R data. The imputation model will include the treatment group, the prognostic baseline characteristics, and ALSFRS-R at baseline. For patients deceased or withdrawn without a post-randomization assessment, the same rules specified for primary analysis will be applied. Moreover, the imputation of missing data under the missing not at random (MNAR) assumption considering the reason for missingness will be carried out using the delta-based MI method. A range of penalties by reason of missingness (study termination due to adverse events AE and death of patients) will be considered. All other missing data will be imputed under MAR assumption, applying a null penalty. For withdrawals without a post-randomization assessment, the same rules specified for primary analysis will be used. A total of 50 imputations for each analysis will be performed, which should provide adequate precision since the amount of missing data is not expected to be large [17]. Results from different imputed datasets will be combined using Rubin’s rule.

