### Sample size

The study was powered to assess the potential benefit of TUDCA compared with placebo on the rate of progression, as measured by the ALS-FRS-R total score. The target number of participants was determined based on the expected proportion of responders. In the original planning, based on data from the phase II study [5], a sample size of 199 subjects per arm was calculated to detect a 10% difference between arms assuming a response rate of 10% in the placebo group. This sample size provides at least 80% power with a two-sided alpha of 5%. Considering a dropout rate of 10% at 18 months, a total sample size of 440 patients was planned. Such a sample size provides 83.3% power to detect a 13% absolute difference in survival (defined as death or respiratory insufficiency) between the two treatment groups, corresponding to a hazard ratio of 0.616, assuming an 18-month survival of 60% in the placebo group. However, due to the impact of the COVID-19 outbreak on recruitment [9], the enrolment was planned to be closed at 320 randomized patients. The reassessed sample size allows us to detect an absolute difference of 11% in the proportion of responders between the TUDCA and the placebo arms. It also provides a power of 80% to detect a 14% absolute difference in survival, corresponding to a hazard ratio of 0.58.

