### Missing data

#### Imputation rules and key sensitivity analyses

In the primary analysis, for each patient, all available ALSFRS-R scores will be included in the linear regression model to estimate the monthly decline. The following rules for handling missing data will be applied: (i) for deceased patients, as death is clearly a poor outcome and there is no consensus on an alternative score, the lowest score (zero) will be assigned at the time of death, and (ii) for withdrawals or LTF patients without a post-randomization assessment of the ALSFRS-R score, the monthly decline of ALSFRS-R will be imputed using the “nearest neighbor” procedure [15]. For each of these subjects, we will identify the five other participants within the same treatment group whose baseline ALSFRS-R scores were closest to the baseline score of the patient. Then, the largest monthly ALSFRS-R decline observed among the identified neighbors (worst-case imputation) will be used for imputation. All missing data will be imputed within treatment groups defined by the randomized treatment assignment. As sensitivity analysis, within the nearest neighbor procedure, the “bestcase imputation” will also be carried out imputing the smallest observed monthly decline.

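### The MNAR multiple-imputation run gives deaths an unsized penalty instead of zero, and the imputation model does not name the lead-in scores that define response

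*SAP article*

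**What the plan says.** For the primary analysis, under Imputation rules and key sensitivity analyses, the article scores deaths explicitly: "the lowest score (zero) will be assigned at the time of death". Patients who withdraw or are lost with no post-randomization score get the worst decline among five neighbours.

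Under Multiple imputation-based sensitivity analyses there are two runs.

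- **MAR run.** The primary rules are kept for patients who died or withdrew with no post-randomization assessment. It is unclear whether that last condition also limits the deceased. The model is given as: "The imputation model will include the treatment group, the prognostic baseline characteristics, and ALSFRS-R at baseline".
- **Delta-based MNAR run.** "A range of penalties by reason of missingness (study termination due to adverse events AE and death of patients) will be considered". For every other reason: "All other missing data will be imputed under MAR assumption, applying a null penalty". The primary rules are kept only for withdrawals with no post-randomization assessment; the deceased are not mentioned. No penalty sizes appear.

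A further MAR run, in the COVID-19 section on missing data in the primary endpoint, covers all missing values and adds infection status and pandemic period to the model. It states no exception for deaths.

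Under Outcomes, response means at least a 20% improvement of the treatment-period slope over the patient's own lead-in slope. Table 1 schedules ALSFRS-R at M-3, W-6 and M0. Baseline Patient characteristics equates baseline with month 0.

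**The concern.** A penalty for missing values should make a run harsher than MAR, and such a run is normally read as a stress test of the primary result. Zero at death is already close to the harshest score available. If the MNAR run replaces it with an imputed trajectory lowered by a finite amount, the run is softer on deaths than the analysis it checks, and agreement between the two says less than it seems to. It also answers a different question, since it assigns function to patients who have died.

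The second issue is the model itself. Each patient's threshold is 80% of that patient's lead-in slope. If the imputation model knows only the month-0 score, imputed values for a fast lead-in decliner are drawn towards the average decline, and that patient passes the threshold too easily.

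**Working it through.** **1. The plan's own figures.** The article gives no figure for the imputation analyses. The sample-size figures that supply inputs do reproduce. For 10% v 20% responders, two-sided 5%, 80% power:

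n = [1.960·√(2·0.15·0.85) + 0.842·√(0.10·0.90 + 0.20·0.80)]² / 0.10² = (0.990 + 0.421)² / 0.01 ≈ 199 per arm, as stated.

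For dropout, 398/0.90 = 442.2 and 398·1.10 = 437.8, and the plan's 440 lies between them. No stated figure is wrong. The assumed 60% 18-month placebo survival counts death or respiratory insufficiency, so 1 − 0.60 = 40% is only an upper bound on placebo deaths.

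**2. One patient by hand.** Assume a lead-in slope of −2.0 points/month (threshold 0.8·(−2.0) = −1.6), a month-0 score of 38, an observed decline of 1.2 per month, and death at month 10. Month 0 is taken as part of the treatment-period fit.

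- *Zero at death:* points (0, 38), (3, 34.4), (6, 30.8), (9, 27.2), (10, 0). Sxy = −197.44, Sxx = 69.2, slope = −2.85. Non-responder.
- *Imputed at months 12, 15, 18 on the same line, less a penalty δ:* over visits 0 to 18, Sxx = 252 and the penalised visits contribute (3 + 6 + 9)·δ = 18δ. Slope = −1.2 − (18/252)·δ = −1.2 − 0.0714·δ. At δ = 5 it is −1.56: responder. At δ = 15 it is −2.27: non-responder.
- The switch is at δ = 0.4/0.0714 = 5.6. If month 0 is left out of the fit, the coefficient is 13.5/157.5 = 0.0857 and the switch is at 4.7.

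The result therefore depends on a penalty size that the article does not give.

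**3. Simulation of deaths.** 320 patients, visits as in Table 1, least-squares slopes, 20% rule, sequential regression imputation, 60 trials with 10 imputations per setting. Assumed: mean decline about 1 point/month, 20% slowing under TUDCA, about 25% placebo deaths, about 9% dropout. Share of deceased patients classed as responders, at residual SD 0.5 / 1.0 / 1.5:

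| Rule | Month-0 score only | Lead-in scores added |
|---|---|---|
| Zero at death | 0.4 / 1.3 / 2.4% | not applicable |
| δ = 5 | 19.2 / 28.6 / 34.2% | 11.6 / 22.4 / 30.4% |
| δ = 10 | 12.7 / 18.7 / 24.5% | 7.1 / 12.9 / 20.4% |
| δ = 15 | 10.6 / 13.7 / 18.0% | 6.9 / 10.1 / 14.7% |

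A further simulation under other assumptions (month-0 model) gave 0–3% under zero at death, 12–34% at δ = 5 and 3–14% at δ = 15. Taken together, the range is about 3–34% against 0–3%.

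**4. Effect on the comparison.** In the tabulated simulation, the placebo response rate rises from 14–28% (zero at death) to 17–36% (δ from 5 to 15, month-0 model). At δ = 5 the arm difference goes from 0.227 to 0.239, 0.156 to 0.157 and 0.112 to 0.110. The odds ratios implied by these average rates go from 3.55 to 3.23, 2.12 to 1.97 and 1.66 to 1.58, a fall of about 5–9%. For example, (0.368/0.632)/(0.141/0.859) = 3.55.

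**5. Lead-in scores.** Response among dropouts with at least one post-randomization visit, at SD 0.5 / 1.0 / 1.5:

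- *Simulation of step 3:* complete data 32.7 / 38.4 / 40.6%, month-0 model 35.4 / 40.4 / 41.2%. Excess 2.7 / 2.0 / 0.6 points. Two further runs with dropout at random gave 1–3 points.
- *Dropout after month 3, likelier with a steeper lead-in slope (15% withdrawing):* true 28 / 46 / 58%, month-0 model 44 / 56 / 66%, lead-in scores added 32 / 46 / 59%. Excess 16 / 10 / 8 points, falling to 4 / 0 / 1.
- *Same pattern, separate run:* true 27 / 45 / 57%, month-0 model 40 / 58 / 66%, lead-in scores added 24 / 44 / 57%. Excess 13 / 13 / 9 points. Another gave 4–9.

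**The case against.** Several stronger readings are tempting and are not supported.

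- *All the imputation analyses turn deaths into responders.* The MAR run of the main imputation section appears to keep zero at death; only the reach of its qualifier is unclear. In the MNAR run the outcome depends on the penalty, and large penalties move the share back towards the primary rule.
- *Dropouts in general become responders.* Withdrawals with no post-randomization score keep the worst-case neighbour rule in both runs. For the others, the bias is small unless dropout follows lead-in decline.
- *The treatment contrast is distorted.* Step 4 does not show this. With a 25% slowing and dropout tied to lead-in slope, the arm difference falls from 31.5 to 29.2 points (30.5 with lead-in scores), which works against TUDCA.
- *40% of placebo patients are affected.* That figure includes respiratory insufficiency; the zero rule covers death alone.
- *The lead-in scores are certainly left out.* The prognostic baseline characteristics are not listed and could include the lead-in slope, and an article may leave the list to the full SAP. This stands, and makes the second part a request to name the variables.

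It can also be said that the article admits there is no agreed score for death, so varying it is legitimate, and that it nowhere requires the MNAR run to be harsher than the primary analysis. That is fair, but a deliberate softening should be announced as such. Finally, the penalty might be meant only for visits missed before death, with zero still assigned at death. The text does not exclude this, but the run's closing sentence, which keeps the primary rules for withdrawals alone, points the other way.

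**Conclusion.** The point holds in a limited form. As written, the MNAR run, and possibly the COVID-19 MAR run, can treat deaths more leniently than the primary analysis: about 3–34% of deceased patients become responders at penalties of 5–15 points, against 0–3%. The penalty sizes, the residual SD and the constant subtraction at each imputed visit are assumptions. The direction was the same at all three residual SDs. The arm difference changes little, so the loss is in what the sensitivity analysis can show, with no demonstrated bias in favour of TUDCA.

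The month-0-only model overstates response among dropouts with a post-randomization visit by about 0–3 points if dropout is unrelated to lead-in decline and roughly 4–16 if it is related. At the planned 10% dropout, the latter moves an overall response rate by about 0.10·4 = 0.4 to 0.10·16 = 1.6 points, before counting any effect on imputed deaths.

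The primary analysis is untouched. Severity is minor to moderate.

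**What to change.** 1. State that zero is assigned at the time of death, and that no score is imputed after it, in every imputation run: MAR, MNAR and the COVID-19 runs.
2. Restrict the delta penalty to discontinuations other than death, and give its range in ALSFRS-R points and how it is applied across visits.
3. Name the M-3, W-6 and M0 scores (or the lead-in slope) and all observed post-randomization scores in the imputation models of both sections, and list the prognostic characteristics.
4. Optional: apply a delta to other withdrawals and losses to follow-up as well. The article plans a tipping-point analysis only for COVID-related missing data and names no arm for it, so extending it is a choice and not a correction.

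The cost is a few sentences in the SAP and a changed imputation call, with no new data. The change should be dated before unblinding, which the plan places after all analyses are done. The sensitivity results may look less favourable in absolute response rates.

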### Supporting analysis

Based on suggestions received from the EMA Scientific Advice Working Party on 28 February 2017, we will also consider a definition of responders with a threshold of 25%. The same model specified for the primary analysis will be applied.

### Additional analyses to account for the COVID-19 pandemic

Prior to the COVID-19 pandemic, the primary analysis was planned using an ITT approach, by properly accounting for missing data and premature study termination. Despite the occurrence of the COVID-19 pandemic, the original primary objective of TUDCA-ALS study remains unchanged, implying that the estimate of TUDCA effect is not confounded by COVID-19 pandemic related disruptions. However, COVID-19-related intercurrent events need to be properly accounted for to ensure an appropriate interpretation of the trial results [18]. Following the recommendation received on December 1, 2022, after the mid-term review of the project by the European Commission, additional sensitivity and supplementary analyses have been planned in accordance with the ICH E9 (R1) Addendum on Estimands and Sensitivity Analysis in Clinical Trials [19].

In application of the COVID-19 amendment, changes have been made to adapt the electronic case report forms for the study visits performed after February 3, 2020. The main changes include the implementation of telemedicine visits, the specification of missing data due to COVID-19, collecting information on COVID-19 protocol deviations, COVID-19 vaccination, and study termination due to COVID-19. Information on COVID-19-related infections, therapy, and death are expected to be reported in the descriptions of protocol deviations, as well as in the form on concomitant medication and adverse events. All these data will be used to perform additional analyses in accordance with the specific EMA guidelines on the implications of coronavirus disease (COVID-19) on methodological aspects of ongoing clinical trials [20].

#### Assessing the impact of COVID-19 pandemic on trial conduction

To describe the impact of COVID-19 pandemic on trial conduction, with the aim of excluding treatment-specific data patterns by reason due to COVID-19, the following analysis will be performed by treatment group. Baseline characteristics will be summarized by the enrolment period categorized in pre-pandemic, pandemic with restrictive measures, and post-pandemic. The number of visits conducted via telemedicine (including audio-visual connections and telephone contacts), missing data, protocol deviations, end of study by reason, COVID-19 infections, concomitant medications for COVID-19, and death due to COVID-19, will be reported overall and by treatment group. A time to occurrence analysis will be conducted for COVID-19-related protocol deviations using Kaplan-Maier curves and the log-rank test.

#### Assessing the impact of the COVID-19 pandemic on treatment effect

Even if self-administered ALSFRS-R collected through telemedicine is a validated approach [21–23], an assessment of the association between on-site and telemedicine visits will be evaluated by comparing the distributions of ALSFRS-R measurements by the modality of visit conduction (in-person or telemedicine) stratifying for treatment group and study visit. The modality of visit conduction will be included in the multivariable LME model for ALSFRS-R as a fixed effect. To assess the impact of the pandemic on the ALSFRS-R slope, the pandemic time-period and the infection status will also be included in the multivariable LME model as fixed effects. The interaction term between treatment and pandemic time-periods will be included, and the treatment effect by pandemic periods will be reported. Additionally, an estimate of treatment effect will be obtained through inverse probability treatment weighting to assess the potential confounding effect of COVID-19 intercurrent events [24].

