### Analysis method for primary and secondary outcomes

In the primary analysis, the effect of treatment on the primary endpoint will be measured by means of the odds ratio estimated through an unadjusted logistic regression model including a dummy variable for treatment group. Moreover, as part of the sensitivity analyses, a multivariable logistic regression model will be performed. Survival outcome will be analyzed using Kaplan–Meier survival analysis and log-rank test. Univariate and multivariable Cox proportional hazards models will also be applied. Additionally, the joint modeling omnibus test [13] will be used to assess the simultaneous effect on ALSFRS-R and survival. The longitudinal secondary endpoints (ALSFRS-R, ALSAQ-40, FVC, EQ-5D scale, MRC scale, and biomarkers) measured on a continuous scale will be analyzed using a multivariable linear mixed effect model (LME) to estimate the mean difference in the rate of decline between TUDCA and placebo over 18 months. The following covariates will be included in the multivariable models: age, gender, type of ALS, and region of initial site of diagnosis.

Country will be included as a random factor in the LME models. Clustered standard errors by country will be used in logistic and Cox regression models to obtain robust estimates. All primary and secondary analyses will be carried out on both ITT and per-protocol populations.

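### The pandemic terms named for the ALSFRS-R mixed model estimate shifts in score level, while the stated aim is the pandemic's impact on the slope

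*SAP article*

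**What the plan says.** The aim and the method stand in one sentence: "To assess the impact of the pandemic on the ALSFRS-R slope, the pandemic time-period and the infection status will also be included" in the multivariable mixed model, as fixed effects. The next sentence adds one interaction: "The interaction term between treatment and pandemic time-periods will be included, and the treatment effect by pandemic periods will be reported".

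The base model is described under 'Analysis method for primary and secondary outcomes'. Its purpose is "to estimate the mean difference in the rate of decline between TUDCA and placebo over 18 months", so it must contain time and treatment by time, although neither is written out. On random effects the article says only: "Country will be included as a random factor in the LME models".

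Pandemic period is not defined for this model. The section on trial conduction uses an "enrolment period categorized in pre-pandemic, pandemic with restrictive measures, and post-pandemic", which is fixed for each patient. The sensitivity analysis for the survival endpoint instead treats pandemic period and infection status as time-dependent.

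**The concern.** The question is whether the pandemic changed the speed of decline. The terms named answer another one: whether scores sit higher or lower at a given time in one period, or after infection. The two can disagree. A period in which patients decline faster need not show a shift in level, and a period that enrolled patients with lower scores shows such a shift without any change in decline.

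At stake is the trial's statement on whether COVID-19 disturbed progression on its main scale. The article's discussion cites reports that the pandemic and the restrictions affected ALS progression, and its conclusion promises to record that influence. A non-significant period term could be reported as no effect on slope when the model had little chance of seeing one.

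**Working it through.** The article gives no power or error rate for these terms, so there is no stated figure to reproduce.

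**Inputs from the article.** 320 randomized patients, 1:1; visits every 3 months from M0 to M18 (7 visits); two-sided 5%; randomization from 20 May 2019 to 4 April 2022 (about 34.5 months).

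**Assumptions not in the article.** Baseline score 38 (SD 5); slope -1.0 point/month (SD 0.6); residual SD 2; uniform accrual; no dropout; restrictions starting 10 months after first randomization and lasting 14 months (4 months also tried, with slope SD 0.4 and 0.6).

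**Step 1: what the terms estimate.** With t for time, Z for treatment and P for period, the model as named is

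E(Y) = b0 + b1·t + b2·Z + b3·Z·t + g·P + d·Z·P (+ covariates).

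Within a period the rate of change is b1 + b3·Z. Neither g nor d appears in it. If P varies by visit, g is a step when the period changes. Adding h·P·t gives a rate of b1 + b3·Z + h·P, and h is the quantity the aim asks for. The same holds for infection status, which has no interaction of any kind.

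**Step 2: check by hand (enrolment coding, patient random intercept and slope, assumed uncorrelated).** Visit times average 9 months, with sum of squares 252. For a patient's fitted intercept a and slope b:

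- Var(a) = 25 + 4(1/7 + 81/252) = 26.86
- Var(b) = 0.36 + 4/252 = 0.376
- Cov(a,b) = -4 × 9/252 = -0.143

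If one slope is forced on all periods, the estimated level difference is Δa - [Cov(a,b)/Var(b)]·Δb = Δa + 0.38·Δb. A slope change of -0.3 therefore appears as -0.11 point, although it accumulates to 0.3 × 18 = 5.4 points at month 18. The patient random slopes absorb the rest.

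Restricted enrolment covers 320 × 14/34.5 = 130 patients, against 190 others. The SE of the level difference is √26.80 × √(1/130 + 1/190) = 0.59, where 26.80 = 26.86 - 0.143²/0.376. The SE of the slope difference is √0.376 × 0.114 = 0.070.

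| Truth | Term tested | z | Power, 2-df test |
|---|---|---|---|
| Slope change -0.3 | period main effect | 0.11/0.59 = 0.19 | 5% |
| Slope change -0.3 | period × time | 0.3/0.070 = 4.3 | 98% |
| Intake difference of 2 points | period main effect | 2/0.59 = 3.4 | 87% |

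**Step 3: simulation.** Mixed model fitted by maximum likelihood with patient random intercept and slope; 2-df Wald test of period; 300 runs per scenario (100 for the 4-month cases). Entries are rejection rates.

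| Period coding; restrictions | Truth | Main effects as written | Plus period × time | Months spent in restrictions |
|---|---|---|---|---|
| Enrolment; 14 months | no change | 4% | 5% | – |
| Enrolment; 14 months | slope -0.2/-0.3/-0.5 in patients enrolled then | 6/5/7% | 72/97/100% | – |
| Enrolment; 14 months | slope -0.2/-0.3/-0.5 in restricted calendar months | 10/20/44% | 33/59/96% | – |
| Enrolment; 14 months | intake difference 2/3 points | 86/100% | 5/4% | – |
| Enrolment; 4 months | intake difference 2 points | 47-48% | 3% | – |
| Visit date; 14 months | slope -0.2/-0.3/-0.5 in restricted calendar months | 5/7/6% | 93/100/100% | 100/100/100% |
| Visit date; 14 months | intake difference 2/3 points | 8/13% | 7/7% | 10/7% |
| Visit date; 4 months | slope -0.3 in restricted calendar months | 64-71% | 11% | 91-92% |
| Visit date; 4 months | intake difference 2 points | 4% | 6-7% | 3% |

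The hand check agrees with the matching rows. Simulation error is about √(0.05 × 0.95/300) = 1.3 percentage points near 5%, and √(0.7 × 0.3/100) = 4.6 points near 70% in the 4-month cases.

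**Step 4: fitting without a patient random slope.** The main effect then reacts to a slope change in 49-100% of runs (enrolment coding, change by enrolment) or 55-98% (visit coding, calendar change). But visit coding rejects in 24% when nothing has changed, and an added period × time term rejects in 56% under the null with enrolment coding. That apparent sensitivity is not usable.

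**The case against.** The strongest reply is that the wording is shorthand. Calling terms fixed effects means only that they are not random, and does not exclude a product with time. The article leaves time and treatment by time to be inferred from the base model's stated target, so the same courtesy could apply here. It condenses a full SAP that is not shown. Because the treatment effect in this model is a difference in rate of decline, treatment by period may mean treatment × time × period, which by the usual hierarchy would bring in period × time.

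Part of this stands: the treatment-by-period term may be meant on the slope, and the text does not settle it. But the sentence pairs a named aim with a named method, and the two do not match. The article does write interactions out where it wants them, here and under 'Subgroup analyses'. Even on the slope, treatment by period asks whether the drug effect differs, not whether progression did. Infection status has no interaction on any reading.

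It is also fair that this is one supplementary model among several. The primary analysis is an unadjusted logistic regression that does not use it, and concurrent 1:1 randomization would be expected to spread a general pandemic effect over both arms.

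A reader might go further and infer that a slope change would be missed almost every time and that an intake difference would be flagged as a matter of course. The documents do not support that. Both hold together only if period means enrolment period and the model has patient random slopes, and the article fixes neither.

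**Conclusion.** The mismatch between aim and method stands and does not depend on any simulation. Followed as written, the model yields level shifts in points and, at most, effect modification; it does not estimate the pandemic's impact on the rate of decline.

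The practical size is uncertain. With patient random slopes, detection of a slope change ranged from about the nominal 5% to 71%, depending on period coding and the length of restrictions. A 2-3 point intake difference was flagged in 86-100% of runs with enrolment coding and 14 months of restrictions (47-48% for 2 points with 4 months), but in only 4-13% with visit-date coding. All these figures rest on assumed SDs, slopes and period dates. The point is worth correcting because the remedy is cheap, but no efficacy conclusion from the primary responder analysis depends on it.

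**What to change.** In the section on the pandemic's impact on treatment effect:

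- State whether pandemic period and infection status are enrolment-based or time-varying in the mixed model, with the dates that bound each period.
- Keep the main effects and add period × time. If period is time-varying, use months accrued in each period instead; with short restrictions the product with visit time does poorly (11% against 91-92%).
- Add a post-infection slope term, such as months since infection.
- Include a patient random intercept and slope. Without the random slope the added terms are not valid tests.
- Write the treatment-by-period term as treatment × time × period if a treatment effect on slope by period is meant.
- Report the slope coefficients with 95% CIs as the pandemic's impact on slope, and do not read the main effects that way.

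The cost is a few sentences of SAP text and a few degrees of freedom in a supplementary model, on data already collected.
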